# Funding

This trial has been funded by a philanthropic grant from the Jack Murphy Memorial Society which is administered by the Hunter Medical Research Institute.

# Background

Cardiopulmonary resuscitation is a skill that is widely taught in the community with varying methodological approaches and varying degrees of success. Despite the concept of lay person CPR training being many well established, the rates of attempted rescue by bystanders in the community remains unacceptably low (*CPR only attempted in 35% of out of hospital cardiac arrests prior to ambulance arrival as per the 2017 NSW Ambulance Service Cardiac Arrest Registry Data*).

Many systems around the world have significantly better uptake of CPR as a lay-person skill with CPR rates doubling our own and, in some cases, survival rates nearly tripling those found in Australia. World leading cardiac arrest response communities such as Seattle and Sweden are implementing new and innovative methods of disseminating CPR training to the wider community, alongside other novel methods of managing the initial resuscitation of a person suffering a cardiac arrest.

It is widely understood that the single most influential factor in whether a person recovers from a cardiac arrest that is within our control is whether or not they receive early CPR. For this to happen in more than 35% of the cases of cardiac arrest in the community, a rapid deployment of community targeted CPR training must be undertaken at a large scale.

An important part of understanding how to best disseminate this message widely is understanding the factors that influence successful CPR teaching to lay people.

# Literature Review

Survival rates for out of hospital cardiac arrest with survival to discharge are low and vary widely depending on global region (3.0% to 9.7%). The extensive geographical variation and poor outcomes associated with OOHCA have remained mostly static in the last three decades (1).

Some regions have worked on optimising the local chain of survival and have reported rates of survival to hospital discharge as high as 40%. The two factors that had the biggest impact on survival were early, good quality, CPR and early defibrillation (2,3). The importance of good quality bystander CPR initiated early in the resuscitation of patients cannot be emphasised enough and the rate of neurologically intact survival to discharge is directly related to this one factor (1, 4).

Internationally Norway (25%) (5), Seattle (21%) (6) and the Netherlands (21%) (7) lead the way with survival of OOHCA. The success in these countries has been attributed to early CPR and defibrillation made accessible through a system wide approach. In Norway, where survival is best with one in four cardiac arrests resulting in a favourable outcome, CPR training has been part of the national school curriculum since 1961.

Bystander CPR has also been closely linked with favourable outcomes, and areas with low socioeconomic status have been shown to have less bystander CPR and therefore reduced survival (1).

In May 2017, 2084 UK adults took part in a survey to help us discover how many people have trained in CPR or PAD use and how willing they are to act if they witnessed an OHCA. One in 5 survey respondents said they had witnessed a cardiac arrest; 58% reported that they had received CPR training and 22% PAD training. Training made a difference in people’s willingness to act. 74% of those trained in PAD use compared to 24% of those untrained said they would be willing to use one. For those trained in CPR, 76% were likely to perform CPR compared to 28% who were untrained. There is potential to increase survival rates through continuing attempts to improve public awareness and uptake of resuscitation skills training (8).

Within Australia, survival to discharge for OOHCA is 7.6% (1). Over the past year a group of local Doctors and Nurses from the Hunter Heart Safe Collaborative have tried to increase community awareness of cardiac arrest and how to manage it from the crucial first few seconds of its occurrence to the point trained ALS providers arrive to assist. This project has thus far, taught hands only CPR to over 2000 community members across the lower hunter region in a bid to improve rates of survival in OOHCA.

In their 2017 paper, Cartledge et al described the introduction of a video-based CPR instruction program into a cardiac rehabilitation group. This project was well received and was deemed effective in the evaluation, but one important finding of this trial was the willingness of the initial recipients of training to share the training with other. While the effectiveness of this secondary training was not assessed during this trial, this concept of peer facilitated training underpins the intervention described in this protocol.

# Aim

The primary aim of this study is to assess the comparative feasibility of a peer facilitated community CPR training model using either traditional face-to-face training or a hybrid training session based around a simple video-based training aid.

It is hypothesized that the efficacy of both initial training methods will be comparable on assessment. However, we anticipate that the introduction to shareable CPR training videos will be more successful in facilitating transfer of knowledge from one participant to the next – thus allowing the teaching to progress further with the aid than without.

# Trial Design

This study will utilise a prospective cohort design to evaluate the feasibility of peer facilitated CPR training provided by community members following either A) a traditional face to face CPR training session OR B) a hybrid model based around a simple video-based training aid.

Groups of 20 participants will be recruited to participate in this study through Hunter Heart Safe training sessions. These larger groups will then be further broken down into 5 ‘streams’ of 4 participants. The first participant in each of the streams (generation 1) will be designated to receive either traditional face to face CPR training OR a hybrid training session based around a simple video-based training aid. The participants will be randomized to either one of the two arms of training blocks based on a computer generated randomized sequence. The four participants following on from the initial trainee in each ‘stream’ are referred to as subsequent ‘generations’ i.e. the second person in a stream constitutes the second generation of that stream, the fourth person in sequence is the fourth generation etc.

Following on from their initial training, the first participants from each stream will then be tasked with teaching the lesson they have learned (one on one) to the second generation. If this message is conveyed successfully, the second generation will be tasked with teaching the third, and so on until either the message fails to be delivered appropriately, or all 4 generations within a single stream have been successfully taught CPR.

***
[figure not shown]
***

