***Graphical Representation of the Study Design***

Following training of the initial participants, peer to peer training within each stream will be attended in separate rooms to avoid cross communication where possible. Once an individual has successfully delivered their training to the next generation in their stream, that person will have completed their participation in the trial. At the completion of the data collection period, a final large group session of conventional CPR training will be offered to all participants as a way of ensuring suitable validated training is offered to all participants.

For one generation to progress from learning to teaching, they must successfully complete an assessment against a ‘critical item checklist’ (as outlined in appendix C). The first generation will be excepted from this assessment as the initial the initial training sessions efficacy is not the primary focus of this trial. If the participant passes this assessment, they are instructed to teach the participant in the next generation of their stream what they have learned over a 20-minute period. If any member of the stream fails the assessment, data collection for that stream ends and all remaining members of that stream are deemed to have completed their participation in this trial. An assessment must be completed by every generation involved in peer facilitated teaching.’

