# Study Size

A purposeful convenience sample will be employed for this trial owing to the feasibility nature and the contingent sequential recruitment model described. These factors together make it impractical for a formal sample size calculation to be attended.

This trial will intend to recruit 160 total participants across 8 groups of 20 possible participants with acknowledgement that the total number of recruited participants is dependent on the outcome of the serial assessments in each group. Recruitment will be shared equally between the traditional face to face CPR training group and the hybrid sessions based on the video training aid. Each group will be randomised to either the traditional face to face or hybrid groups electronically with the assignment being concealed in an opaque envelope which will be opened immediately prior to the commencement of the session.

While all efforts to maximise recruitment to ensure full groups of 20 will be taken, it is acknowledged that there may be attrition leaving some groups slightly short of the 20 participants. These details and reasons for the shortages will be reported along with the trial findings.

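### Two sections of the protocol name different units of randomisation, and the planned binomial comparison ignores the group-level allocation that the operational text describes

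*Protocol*

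**What the plan says.** Trial Design describes groups of 20 and then says: "These larger groups will then be further broken down into 5 ‘streams’ of 4 participants". It continues: "The first participant in each of the streams (generation 1) will be designated to receive either traditional face to face CPR training", or the hybrid session. The next sentence is the randomisation statement: "The participants will be randomized to either one of the two arms of training blocks based on a computer generated randomized sequence". It gives no procedure beyond the computer-generated sequence.

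Study Size gives the numbers: "This trial will intend to recruit 160 total participants across 8 groups of 20 possible participants". It then sets out a different unit: "Each group will be randomised to either the traditional face to face or hybrid groups electronically", with the assignment "concealed in an opaque envelope which will be opened immediately prior to the commencement of the session". Recruitment is to be shared equally between the arms.

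The section under the design figure keeps streams in "separate rooms to avoid cross communication where possible" and exempts generation 1 from assessment, so a stream yields at most three assessments and stops at the first failure.

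Statistical Methods compares the arms by a binomial test of proportions with 95% intervals. It adds a two-sided 90% interval whose upper limit must fall below 0.15 for non-inferiority. It mentions no unit of randomisation and makes no allowance for group or stream.

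**The concern.** A sequence for participants and a sequence for groups are different designs. They need different allocation lists and envelopes, and they support different analyses. The Study Size text puts everyone in a session in the same arm, so the arms differ by session as well as by training. Groups are community classes or volunteers from a research database, met in varying venues, so some variation between sessions is plausible. A test that counts each assessment as an independent observation then attributes session differences to training. The 0.15 rule depends directly on the width of the interval, so an interval that is too narrow bears on the declared conclusion as well as on the p value.

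**Working it through.** **1. Planned numbers.** From Study Size and Trial Design: 8 groups × 20 = 160 participants, which reproduces the stated total. Each group has 5 × 4 = 20 people, so there are 8 × 5 = 40 streams. With generation 1 not assessed, the maximum is 40 × 3 = 120 assessments, or 60 per arm and 15 per group. There is no power calculation to reproduce, because the protocol says none was made.

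**2. Units randomised under each reading.**

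| Reading | Units | Per arm | df, unit-level t-test |
|---|---|---|---|
| Group (Study Size) | 8 | 4 | 8 − 2 = 6 |
| First trainee or stream (inferred from Trial Design) | 40 | 20 | 40 − 2 = 38 |

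**3. Design-effect check.** DE = 1 + (m − 1) × ICC. The true one-sided error of an unadjusted nominal 5% test is 1 − Φ(1.645/√DE). The ICC values are assumed.

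| ICC | DE, group (m = 15) | Effective n per arm (60/DE) | One-sided error | DE, stream (m = 3) | One-sided error |
|---|---|---|---|---|---|
| 0.01 | 1.14 | 52.6 | 6.2% | 1.02 | 5.2% |
| 0.05 | 1.70 | 35.3 | 10.4% | 1.10 | 5.8% |
| 0.10 | 2.40 | 25.0 | 14.4% | 1.20 | 6.7% |
| 0.20 | 3.80 | 15.8 | 19.9% | 1.40 | 8.2% |

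These use the maximum number of assessments. Chains stop at failure, so for each ICC they are upper bounds.

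**4. Simulation that respects early stopping.** The inputs were 8 groups × 5 streams, a pass probability of about 70% per generation, a stream SD of 0.5 on the logit scale, chains stopped at first failure, no true arm effect, and 4,000 trials per scenario. About 87 assessments occur per trial. Rejection rates at nominal two-sided 5%:

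| Between-group logit SD | Binomial test, groups randomised | Binomial test, streams randomised | t-test on group means, 6 df |
|---|---|---|---|
| 0 | about 5–6% | about 6% | about 5% |
| 0.5 | about 11% | about 6% | about 5% |
| 0.8 | about 16% | about 6% | about 5% |

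**5. Interval width.** At a 70% pass rate a stream yields on average 1 + 0.7 + 0.7² = 2.19 assessments, so 20 × 2.19 = 43.8 per arm. The standard error of the difference is √(2 × 0.7 × 0.3/43.8) = 0.098. The 90% half-width is 1.645 × 0.098 = 0.16 with the normal quantile and 1.943 × 0.098 = 0.19 with t on 6 df. The second figure assumes no variation between groups; any such variation widens it further.

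**The case against.** The best defence is that the documents lean one way. Study Size is the only section with a procedure staff could carry out, and it refers to hybrid sessions. The timetable under Participants has a single initial-training slot and attaches the control condition to a group. Harms speaks of allocation by group. The loose phrase about arms of training blocks in Trial Design could itself mean sessions. The design figure is not shown and might settle the point. All of this stands: group allocation is the likelier intention. It does not remove the conflict, because no available sentence states it and Trial Design still says participants.

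A reader might infer from Trial Design that 40 streams are randomised and that both arms share a session, so that cross-talk contaminates the comparison. The documents do not support that as a stated fact. Streams are never named as the randomised unit; that is an inference from the sentence about generation 1. Keeping streams in separate rooms also makes sense when all of them are in one arm. Contamination between arms is a risk only if the investigators do intend mixed sessions.

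Two further points limit the weight of the concern. Outcomes lists the between-arm comparison as secondary, the primary measure being the count of passes across all groups; against that, the aim and Statistical Methods give the comparison prominence. An analysis plan not shown here could also add a cluster adjustment. But the protocol does more than stay silent: it fixes a test and an interval rule that do not suit the allocation it describes.

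**Conclusion.** The concern holds for the wording conflict and for the mismatch between group allocation and the binomial analysis. With 8 randomised units, the false-positive rate of the planned test is close to nominal if sessions do not differ, and rises to about 11% and 16% at between-group logit SDs of 0.5 and 0.8. Those figures rest on assumed values for the pass rate, the stream SD and the group SD; the protocol supplies none of them, so the direction is firm and the size is not. If streams were the unit, the inflation in these scenarios would be mild, at about 6%, so the serious harm arises under the Study Size procedure. The unit should be settled before any envelope is prepared, since no analysis can repair an allocation carried out two ways.

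**What to change.** Reword Trial Design to match Study Size, for instance: *Each group (session) is randomised; all five streams in a group receive the same arm.* Describe the design as cluster-randomised instead of as a prospective cohort. In Statistical Methods, replace the pooled binomial comparison with one on group-level summaries (8 values, t with 6 df) or an equivalent small-sample mixed model, and base both the 95% and the 90% intervals on it.

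If the investigators do intend to randomise streams, Study Size must say one envelope per stream and the analysis must account for stream and session. The protocol should then also address contamination between arms within a session, because rooms are separated only where possible.

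The cost is wording, a changed analysis and wider intervals, with no extra participants. At about 44 assessments per arm the 90% half-width is already about 0.16, above the 0.15 margin, and it becomes at least about 0.19. Non-inferiority is therefore unlikely to be shown at this size unless the hybrid arm is observed to do better, and the protocol should say so.

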***Graphical Representation of the Study Design***

Following training of the initial participants, peer to peer training within each stream will be attended in separate rooms to avoid cross communication where possible. Once an individual has successfully delivered their training to the next generation in their stream, that person will have completed their participation in the trial. At the completion of the data collection period, a final large group session of conventional CPR training will be offered to all participants as a way of ensuring suitable validated training is offered to all participants.

For one generation to progress from learning to teaching, they must successfully complete an assessment against a ‘critical item checklist’ (as outlined in appendix C). The first generation will be excepted from this assessment as the initial the initial training sessions efficacy is not the primary focus of this trial. If the participant passes this assessment, they are instructed to teach the participant in the next generation of their stream what they have learned over a 20-minute period. If any member of the stream fails the assessment, data collection for that stream ends and all remaining members of that stream are deemed to have completed their participation in this trial. An assessment must be completed by every generation involved in peer facilitated teaching.’

# Study Setting

This study will be attended in the community using groups of participants volunteering to participate as a part of a scheduled community CPR training class delivered by the Hunter Heart Safe Group. Some sessions may be run in non-clinical areas within John Hunter Hospital or the Hunter Medical Research institute where suitable community locations cannot be sourced for the trainee group.

# Participants

In order to participate in this study, all participants must meet the following eligibility criteria:

- Age between 18-85 years
- No physical or medical limitation to performing chest compressions for 1 minute
- Must not have attended CPR training in the past 5 years

Participants for this study will be recruited from the pool of community members requesting to receive training from the Hunter Heart Safe group. Where recruitment to the trial is intended, groups will be approached with a recruitment email attached as appendix G. Along with the recruitment email, potential participant groups will be supplied with the participant information form attached below as appendix A.

In addition to participants from the general public, a number of participants may be sourced from the HMRI volunteer database. These volunteers will be engaged through the HMRI volunteer liaison through the delivery of the email invitation attached as appendix H along with the participant information form.

All participants taking place in this study will be provided with a $20 electronic gift card upon completion of their participation (i.e. at the end of the session).

The full timeline of each individual group session is outlined in the table below, noting that this example included the longest possible period required for participants to attend (assuming at least 1 stream makes it through 4 generations of assessment). Where no participants can progress to the next generation of training / assessment, the session will be completed early and where feasible the concluding training session may be brought forward in time to accommodate the needs of the participants.

| **Timeline for session** | **Activity** |
| --- | --- |
| **20 minutes (0:00-0:20)** | Introduction and consent process |
| **20 minutes (0:20-0:40)** | Initial Training for generation 1 (except in control group) |
| **20 minutes (0:40-1:00)** | Generation 1 attempt training of generation 2 |
| **20 minutes (1:00-1:20)** | Assessment of Generation 2 |
| **20 minutes (1:20-1:40)** | Successful Generation 2 attempt training of generation 3 |
| **20 minutes (1:40-2:00)** | Assessment of Generation 3 |
| **20 minutes (2:00-2:20)** | Successful Generation 3 attempt training of generation 4 |
| **20 minutes (2:20-2:40)** | Assessment of Generation 4 |
| **20 minutes (2:40-3:00)** | Final group training session (optional) |
| **Session concluded** | |

# Outcomes

The primary outcome being investigated in this study:

1. Can secondary learner driven peer to peer CPR training be delivered following an initial training session supported by CPR training videos:

- The primary measurement will be the raw number of successful CPR assessments (using the critical item checklist after a peer facilitated training episode) across all training groups.

The secondary outcome being investigated in this study:

1. Is a hybrid CPR training session using simple video-based training aids more effective than traditional face to face training:

- The primary measurement will be the comparative raw number of successful CPR assessments (using the critical item checklist after a peer facilitated training episode) between the face to face and hybrid CPR groups.

# Data Sources / Measurements

The following data sources will be used for assessment:

1. Can secondary learner driven peer to peer CPR training be delivered following an initial training session supported by CPR training videos:

- Assessment data will be collected from every participant following training. This assessment will utilise a critical item checklist (Appendix C), from which the participant must achieve each of the following goals to be deemed ‘successful’ in their assessment:
  - The participant must identify that the patient is unconscious and not breathing
  - The participant must call for help including a phone call to 000
  - The participant must commence CPR correctly (*2 hands on mid chest etc.*)
  - The participant must achieve a Laerdal ‘QCPR Performance Score’ of >50% over a 1-minute period (*as measured using the Laerdal resusci-annie mannequins using the adult compression only parameters*) – This scoring metric is explained in further detail in Appendix D.

